### The Metaverse condition

For the Metaverse intervention condition, the Intake session provides an overview of the foundational principles guiding the utilization of the Metaverse as a platform for delivering support group sessions, and technical issues are addressed. Throughout the program, participants are prompted to share feedback during each session’s Check-in phase, highlighting any challenges or technical issues they may have encountered, which are promptly addressed.

### Generic description of the Metaverse condition

The participants in the Metaverse condition gather in a virtual city square in the city of Kyiv, close to Kyiv’s House with Chimaeras (see Fig. 1).

**Fig. 1 Fig1:**
[figure not shown]
Metaverse meeting place (also see videoclip in the supplementary materials)

### Characteristics of the Metaverse

Participants have the freedom to move around, take seats, and adjust their proximity to other attendeesThey can send private chat messages directly to the facilitatorParticipants have the option to interact with others by moving closer or further awayThey are free to make their seating arrangements and adjust as needed throughout the session

The Metaverse platform we utilize is accessed via a provided hyperlink, accessible through any browser on mobile or PC. Participants are directed to a registration/login interface upon clicking the link. Participants can leave sessions at any time, with their presence shown on the “online users” interface. Voice communication is proximity-based, with silent rooms available for private discussions. Access to the metaverse outside of sessions is controlled through a whitelist feature.

### The Waitlist

Participants in the Waitlist undergo the same set of assessments (minus those that tap into working alliance), under the same schedule as the active groups, after which time they will be given the possibility to join in-person group sessions.

### Outcomes and measures

#### Primary outcomes

The primary outcomes are the levels of depressive symptomatology and anxiety. We assess these outcomes by measuring changes in the total score from baseline to post-intervention. Specifically, we evaluate changes in the total scores of standardized assessment tools for depression and anxiety administered at baseline and post-intervention assessments.

#### Secondary outcomes

Well-being, gender-based violence awareness, and perceived social support constitute the secondary outcomes.

#### Measures

The instruments were translated into Russian, which is the most commonly used language within the Ukrainian refugee community in Romania. The translation process involved the standard back-translation method, and two native Russian speakers were engaged to ensure accuracy.

#### Screening measures

*The DSM-5-TR Level 1 Cross-Cutting Symptom Measure* is a self- or informant-rated measure that assesses important mental health domains across psychiatric diagnoses [30]. The adult version of the measure consists of 23 questions that assess 13 psychiatric domains, including depression, anger, mania, anxiety, somatic symptoms, suicidal ideation, psychosis, sleep problems, memory, repetitive thoughts and behaviors, dissociation, personality functioning, and substance use. Each item asks about how much (or how often) the individual has been bothered by the specific symptom during the past 2 weeks. Each item on the measure is rated on a 5-point scale (0 = none or not at all; 1 = slight or rare, less than a day or two; 2 = mild or several days; 3 = moderate or more than half the days; and 4 = severe or nearly every day).

*The experiences of the war and symptoms of trauma list of events* [31] is used to screen the war-related stressors. The scale has been validated in the study by Karatzias et al. [31]. The measure lists 34 war-related events (e.g., “I heard air raid sirens”), and participants are asked to indicate on a dichotomic—Yes (1) or No (0)—basis (scores range from 0 to 34) if they had experienced each event. As Karatzias et al. [31] instructed, participants are given the following instructions: “We wish to ask you about different things you may have experienced during the war. Below are descriptions of events that you may have experienced following the Russian attack on Ukraine on February 24th, 2022.” If exposed to multiple events, participants are asked to indicate the experience they found more distressing [31]. Higher scores reflect higher levels of war-related experiences.

#### Measures of primary outcomes

*The PHQ-9* [32] is used to assess the depressive symptomatology. The measure is a nine-question instrument designed to correspond to the *Diagnostic and Statistical Manual of Mental Disorder, Fourth Edition, Revised Text (DSM-IV-TR)* diagnostic criteria for major depressive disorder. Participants assign ratings on a scale of 0 to 3 based on how often they experienced specific items in the preceding 2-week timeframe (0—not at all; 3—nearly every day). The scores indicate the severity of depression, ranging from no depression to mild, moderate, moderately severe, or severe depression.

*The GAD-7* [33] is used to assess the severity of generalized anxiety disorder. The measure is a 7-question self-reported instrument designed to correspond to some of the *Diagnostic and Statistical Manual of Mental Disorder, Fifth Edition* diagnostic criteria for GAD. Participants assign ratings on a scale of 0 to 3 based on how often they experienced specific items in the preceding 2-week timeframe (0—not at all; 3—nearly every day). The scores indicate the severity of anxiety, ranging from minimal anxiety to mild, moderate, and severe.

#### Measures of secondary outcomes

*The Multidimensional Scale of Perceived Social Support (MSPSS; *[34]*)* is used to assess the Perceived Social Support. The questionnaire is a 12-item self-report instrument with items measured on a 7-point Likert scale (0—very strongly disagree; 7—very strongly agree). Participants are asked to indicate their preference for each statement provided in the measure. The statements refer to 3 subdomains—Significant Other, Family, and Friends (e.g., “There is a special person in my life who cares about my feelings.”)—and the scores can be calculated both for each subscale and as a total.

The *World Health Organization—Five Well-Being Index* (WHO-5; WHO, 1998) is used to assess the well-being of participants. The measure is a 5-item instrument consisting of statements that the respondents rate on a 6-point Likert scale (0—at no time; 5—all of the time). The statements are rated in relation to the past 2 weeks. The raw scores range from 0 to 25 and are multiplied by 100 to give the final score which ranges from 0 (the worst well-being) to 100 (the best well-being).

Gender-based violence awareness is assessed through 5 general knowledge questions about GBV. Participants will be asked to indicate the correct answer from a list of statements. Each correct answer receives 1 point. The total score ranges from 0 (no GBV awareness at all) to 5 (aware of GBV). The questions were developed in collaboration with an NGO focused on gender-based violence promotion among Ukrainian refugees.

#### Other measures

*Demographics* are collected through questions related to age, sex, gender, place of birth, country of displacement, assistance received while in the host country, marital status, and educational level. Questions regarding whether a family member died in the war, or the timeframe of arrival in the host country are also addressed. In the demographic section, questions concerning previous/actual involvement in therapeutic interventions and previous/actual mental disorders are also included.

The *Working Alliance Inventory – Short Form* (WAI-SR; [35]) was modified and is used to assess the therapeutic alliance within intervention groups. The measure is a 5-point Likert (1—Seldom; 5—Always) instrument consisting of 12 statements related to the relationships between client and therapist. For the present study, 6 items were adapted and are used to assess the alliance between support group facilitators and participants. These items pertain to the agreement on goals (e.g., “My support group leader and I agree on what is important for me to work on”), agreement on tasks (e.g., “My support group leader helps me to do what’s necessary to improve my situation”), and bond (e.g., “I feel comfortable working with my support group leader”), with each subdomain consisting of 2 questions.

#### Others

*The National Stressful Events Survey PTSD Short Scale* (NSESSS; APA, 2013) is a 9-item self-report on a 5-point Likert scale to assess post-traumatic stress disorder symptomatology.

### Participant timeline

Potential participants are assessed for eligibility through an initial assessment phase conducted by phone calls. If the inclusion criteria are met, written consent for participation in the study is obtained. After the initial assessment, the participants meeting the inclusion criteria are randomly assigned to one of the three conditions: (1) Metaverse Condition, (2) In-Person Condition, and (3) Waitlist condition (see flow diagram in Fig. 2). After the initial assessment, the subsequent measures consist of the instruments provided in the “Outcome measures” section. The participants are then randomized by a research assistant without being informed about their group allocation. A priori randomization is performed with a designated computer software (http://www.randomizer.org). Participants who do not meet the criteria for the study are referred to the appropriate entities and structures.

**Fig. 2 Fig2:**
[figure not shown]
CONSORT flow diagram [36] showing subject allocation to the intervention conditions

The study’s assessment and session timings are as follows: The baseline assessment session is delivered at enrollment, serving as the initial evaluation point. Between the baseline and the first session, approximately 1 to 2 weeks elapse. Subsequent sessions are held weekly thereafter. The mid-intervention assessment occurs after the second session but before the third, either on the day of the third session or 1 day prior. Similarly, the final assessment takes place after the fifth session, either on the same day or 1 day after. Additionally, a follow-up assessment is conducted 3 months after the conclusion of the intervention. In-person sessions are held at one of the NGO collaborators’ offices, providing a conducive environment for participant engagement and support.

#### Sample size

An a priori power analysis based on a medium effect size estimation [37, 38] indicated that a total of 45 participants are needed (planned main statistical test is ANOVA repeated measures, within-between interaction; *f* = 0.25; statistical power = 0.95; *α* error probability = 0.05; three groups, four main measurements (pre-intervention, mid-intervention, post-intervention, and follow-up). Power analysis was computed using the G*Power 3.1 program [39].

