The improvement in the mental health and well-being scores within and between the groups will be examined using mixed-effects linear regression with a random intercept and slope over time (three assessments: baseline, after session 2, and post-treatment) and fixed effects for treatment assignment. The 3-month follow-up data will be analyzed using linear mixed effects model that incorporates random intercepts for participants and facilitators. Additionally, we may consider including random slopes for time if the data structure warrants it. If ICC analyses will indicate the presence of a hierarchical structure, we will proceed with conducting multilevel analyses. In addition, we will incorporate fixed effects for time and intervention condition and include any necessary covariates. We intend to perform longitudinal analyses in order to ascertain the long-term effects of the intervention. To evaluate changes in outcome measures from the initial measurement to each subsequent assessment, we plan to employ repeated measures ANOVA, where the data is complete, or mixed effects models, where data is incomplete. Moreover, we acknowledge that the linear mixed-effects model allows for the inclusion of covariates (we plan to control for demographics), and this flexibility makes it a robust alternative to repeated measures ANOVA, especially in complex datasets. The use of covariates was taken into account appropriately in the mixed-effects model, which is another reason we plan this approach when dealing with missing or incomplete data. The results of the other measures—demographic variables and therapeutic alliance as potential moderators and mediators—will be examined in an exploratory manner, utilizing regression models or mediation analyses. The error probability and the issue of multiple testing will be addressed either by employing the Bonferroni correction or the false discovery rate correction. Missing data—over 5%—will be handled with multiple imputation methods. Oversight and monitoring of the data collection process is conducted by the principal investigator and the project manager. Check-in regular meetings are held to review the progress of data collection, address any issues that may arise, and ensure compliance with the study protocol and ethical guidelines.

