There are, nonetheless, several limitations that must be acknowledged. First, as with many clinical trials testing psychological interventions, psychotherapist blinding is not possible. To minimize possible biases, the principal investigator and the project manager are not involved in any support group sessions. Second, the efficacy of virtual support groups may be influenced by the availability and accessibility of technology (e.g., familiarity with virtual platforms, access to a stable internet connection, etc.). To minimize the risk, participants receive technical assistance through the study and a short introduction on how to use the platform is in place. Third, virtual interventions might face higher rates of attrition and dropout compared to in-person. We monitor and report attrition rates and will conduct sensitivity analyses to assess the impact of dropouts on the results. Nevertheless, we acknowledge that, while Metaverse anonymity comes with several benefits, it can have some limitations for some people (e.g., participants not feeling comfortable not knowing who they are speaking to, maintaining confidentiality, whether the team can know for sure who is accessing the Metaverse platform). To minimize the risks, we have implemented several measures to ensure participant comfort and confidentiality within the Metaverse platform. Firstly, participants have the opportunity to meet the trainer before the sessions, either online or in-person, providing them with the opportunity to establish a rapport and familiarize themselves with the facilitator. Secondly, to ensure that the team can verify the identity of participants accessing the Metaverse platform, each participant is given a unique access code. This code is exclusively available to the participant and serves as a secure identifier when accessing the platform. By providing participants with individualized access codes, we can accurately track and monitor participation while maintaining confidentiality and ensuring that only registered participants have access to the sessions.

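### The stated power of 0.95 with 45 participants belongs to a four-occasion omnibus interaction, not to the baseline-to-post primary outcomes or the three-occasion model, and it leaves out the promised multiplicity correction

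*Protocol article*

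**What the plan says.** All references are to the protocol article.

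- **Sample size.** The calculation "indicated that a total of 45 participants are needed (planned main statistical test is ANOVA repeated measures, within-between interaction"), with f = 0.25, "statistical power = 0.95", alpha 0.05, three groups and four measurements, the last being the 3-month follow-up. The software is G*Power 3.1. The correlation between measurements and the sphericity setting are not given.
- **Primary outcomes.** There are two, depressive symptoms and anxiety: "We assess these outcomes by measuring changes in the total score from baseline to post-intervention".
- **Data collection, management, analysis.** Improvement within and between groups is examined in a mixed model over "three assessments: baseline, after session 2, and post-treatment". The 3-month follow-up has its own model. Repeated measures ANOVA is also planned for change from the first measurement to each later one where data are complete. Multiple testing is to be handled "either by employing the Bonferroni correction or the false discovery rate correction".
- **Discussion.** Among the limitations, "virtual interventions might face higher rates of attrition and dropout compared to in-person". The Sample size section makes no allowance for loss.

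**The concern.** Three sections describe three different time structures: four visits for the power calculation, two for the primary outcomes and three for the main between-group model. A power figure belongs to one test and one set of assumptions. Attached to the trial as a whole, 0.95 will be taken as the power for the primary outcomes, and the article does not show that.

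The calculation also uses a single test at alpha 0.05, although there are two primary outcomes and a correction is promised. An omnibus interaction across three arms is, moreover, not the comparison that the Objectives section is about, which is how the Metaverse groups fare, including against Waitlist.

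The stake is interpretation. A reader who believes that power was 0.95 will take a non-significant primary result as good evidence that there is no effect. The risk is greater because the Trial design section describes an equivalence framework.

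**Working it through.** **Inputs.** From the Sample size section: k = 3 groups, N = 45 (15 per arm if equal), f = 0.25, alpha = 0.05 and m = 4 visits. Assumed, because not stated: r = 0.5 between visits and sphericity (epsilon = 1). These assumptions are not arbitrary. With epsilon = 1, the smallest N for 0.95 on four visits is 53 at r = 0.4, 44 at r = 0.5 and 36 at r = 0.6. Only r = 0.5 leads to 45, once 44 is rounded up to equal arms.

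**Formula.** Noncentral F with λ = f² × N × m / (1 − r), df1 = (k − 1)(m − 1) and df2 = (N − k)(m − 1).

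**Step 1: the plan's own figure.** m = 4: λ = 0.0625 × 45 × 4 / 0.5 = 22.5, df 6 and 126, power 0.955. The stated N and power reproduce.

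**Step 2: the other time structures, with f = 0.25 and r = 0.5 kept.**

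| Visits | λ | df | Power, alpha 0.05 | Power, alpha 0.025 |
|---|---|---|---|---|
| 4 (as powered) | 22.5 | 6, 126 | 0.955 | 0.921 |
| 3 (main model) | 16.875 | 4, 84 | 0.911 | 0.854 |
| 2 (primary outcomes) | 11.25 | 2, 42 | 0.834 | 0.747 |

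The last column is Bonferroni over the two primary outcomes (0.05 / 2). A false discovery rate procedure would cost less.

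**Step 3: sensitivity to r** (f = 0.25, N = 45, alpha 0.05).

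| r | 2 visits | 4 visits |
|---|---|---|
| 0.3 | 0.69 | 0.85 |
| 0.4 | 0.76 | 0.91 |
| 0.5 | 0.83 | 0.96 |
| 0.6 | 0.91 | 0.99 |
| 0.7 | 0.97 | 1.00 |

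At r = 0.7 two visits would exceed 0.95, but the plan's own four-visit calculation would then have asked for only 28 participants.

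**Step 4: sensitivity to the time profile.** Here f depends on the whole pattern of means over time, so f = 0.25 on four visits and f = 0.25 on two are in general different true effects. Suppose instead that both active arms improve equally and the effect is scaled so that the four-visit f is 0.25 (r = 0.5, N = 45, alpha 0.05).

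| Share of full effect at baseline, mid, post, follow-up | Two-visit power |
|---|---|
| 0, 1/3, 2/3, 1 | 0.74 |
| 0, 0, 1, 1 | 0.83 |
| 0, 1, 1, 1 | 0.93 |
| 0, 0.4, 1, 1 | 0.94 |
| 0, 0.5, 1, 1 | 0.95 |
| 0, 0.5, 1, 0.7 | 0.98 |

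**Step 5: what f = 0.25 means on two visits.** If both active arms shift by δ (in SD units) at post and Waitlist does not, f = δ / √18. Then f = 0.25 gives δ = 0.25 × 4.243 = 1.06 SD.

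**Step 6: Metaverse versus Waitlist, 15 per arm.** For a two-sided t test at 0.05 with 28 df, the noncentrality is d × √(15/2), and 80% power needs d = 1.06. At r = 0.5 the SD of a change score equals the SD of a single score, √(2 × (1 − 0.5)) = 1, so this also holds for change scores. Adjusting for baseline multiplies it by √(1 − 0.5²) = 0.866, giving about 0.92 SD.

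**Step 7: dropout, as an illustration only.** The documents give no rate. For an assumed 10%, 20% or 30% loss (N = 40, 36 or 31 completers), two-visit power is 0.78, 0.73 or 0.65 at alpha 0.05, and 0.68, 0.62 or 0.53 at alpha 0.025.

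**The case against.** The strongest reply is that nothing is miscalculated. The Sample size section names its test, effect size, alpha, groups and number of measurements, and 45 follows from them. That stands: a reader might infer an arithmetic error in N, and there is none.

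Second, 0.83 is not the one true power for the primary outcomes. It keeps f at 0.25 while the number of visits changes, which matches a profile with no effect at mid-intervention and a full, sustained effect afterwards. Under other profiles two-visit power is higher, and under one it exceeds 0.95. This also stands. The article gives no profile, so it does not support saying that power for the primary outcomes simply is 0.83, or that it must fall below 0.95. What it does support is that 0.95 has not been shown for them.

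Third, the cost of multiplicity and dropout can be overstated. Bonferroni is only one of the two options offered. The Discussion says that attrition might be higher, not that a given rate is expected. Mixed models, multiple imputation, sensitivity analyses for dropout and extended recruitment are all planned, so counting completers only is pessimistic. All of this stands. The multiplicity point survives even so, because the four-visit test itself drops to 0.92 at alpha 0.025.

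Fourth, a reader might conclude that the trial has only 26% power for Metaverse versus Waitlist. That figure takes d = 0.5 at 15 per arm, a value that the article never states. The detectable difference in step 6 is the safer statement.

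**Conclusion.** The concern holds as a mismatch between the test that was powered and the endpoint that was declared primary. The 0.95 applies to a four-visit omnibus interaction with r = 0.5, sphericity, one test at alpha 0.05 and full retention. It is not established for the two baseline-to-post primary outcomes or for the three-visit between-group model, and it takes no account of the promised correction.

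On the article's own f and the r that reproduces its N, the type II error for the primary comparison is about 17% rather than 5%, and about 25% at alpha 0.025. These figures are conditional on the time profile and the correlation, within the ranges in steps 3 and 4. Less dependent on those assumptions is the limit set by 15 participants per arm: a direct comparison of Metaverse with Waitlist can reliably detect only a difference of roughly one SD.

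**What to change.** Keep N = 45 and change the text.

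1. Reconcile the Sample size, Primary outcomes and analysis sections, so that it is clear which visits enter the primary comparison.
2. State that 0.95 refers to the four-visit omnibus interaction with r = 0.5, sphericity, unadjusted alpha and no loss.
3. Restate the power for the baseline-to-post comparison at the corrected alpha, with its assumptions: about 0.83, or 0.75 at alpha 0.025, if f = 0.25 and r = 0.5 are kept. Give the range over r and time profile, and label any dropout figure as an assumption.
4. State that Metaverse versus Waitlist has 80% power only for about 1.06 SD (about 0.92 SD baseline-adjusted at r = 0.5), and that non-significant results will be reported with confidence intervals and not read as evidence of no effect.

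The cost is a less favourable stated power. No extra enrolment and no change to conduct is needed.

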The Intake aims to assess participants if they are eligible for the study and introduce them to the goals of the program. The baseline assessment is conducted before the first session. A step-by-step guide about accessing and completing the survey is provided. Clarification of any questions or concerns are addressed. Session 1 focuses on facilitating an open discussion on participants’ needs, challenges, and cultural adjustment issues. It aims to create a safe and inclusive environment where participants can share their thoughts, concerns, and experiences, setting the tone for the support program. Session 2 focuses on the overall well-being of Ukrainian refugees and introduces strategies to enhance it. Session 3 focuses on perceived social support aiming at shedding light on its significance in our lives and providing practical tools to strengthen and enhance social networks. Session 4 focuses on mental health, with the aim of deepening participants’ understanding of mental health, reducing stigma surrounding mental health issues, and equipping them with essential knowledge and skills for promoting mental well-being. Session 5 is dedicated to raising awareness about gender-based violence (GBV), its various forms, and its profound impact on individuals and communities. Each session typically consists of 6 to 8 participants. The same 6–8 participants will attend each group session for the specific arm to which they are allocated. Each group will interact with the same members consistently from the first session to the last. Each arm is expected to have a minimum of two groups, and the formation of groups begins once a minimum of six participants have enrolled.

These groups convene weekly. To ensure that participants who miss a session are kept up to date, a briefing is conducted at the beginning of each session. This briefing provides a summary of the previous session’s discussions and activities, allowing all participants to stay informed and engaged, even if they were unable to attend the previous session.

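### The stated 0.95 power with 45 participants assumes independence within support groups; with a positive within-group ICC, a valid test has less, by an amount the protocol does not allow for

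*Protocol article*

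**What the plan says.** The Sample size section (Protocol article, Methods) bases the number on "An a priori power analysis based on a medium effect size estimation". It uses f = 0.25, alpha 0.05, three arms, four measurements and "statistical power = 0.95", computed in G*Power 3.1. The result is that "a total of 45 participants are needed (planned main statistical test is ANOVA repeated measures, within-between interaction". No ICC, design effect or group term is listed, and the correlation between occasions is not given.

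The Interventions section sets a typical group size of 6 to 8 and fixes membership: "Each group will interact with the same members consistently from the first session to the last". It adds: "Each arm is expected to have a minimum of two groups". The section on the Waitlist gives that arm assessments only until the comparison is over. Trial design states equal allocation.

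On analysis, the protocol says: "If ICC analyses will indicate the presence of a hierarchical structure, we will proceed with conducting multilevel analyses". The follow-up model names participants and facilitators as random effects, not support groups.

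**The concern.** Participants in a closed support group share members, a facilitator and five weeks of mutual feedback, which the protocol makes part of every session. Correlated outcomes within a group are therefore plausible. The analysis section allows for that possibility; the power statement does not.

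Modelling the groups in the analysis does not restore the power. A valid test then carries the between-group variance and has few group-level degrees of freedom. Ignoring the groups keeps the nominal power only by inflating the type I error: in simulation, the unadjusted ANOVA rejected a true null in 8-15% of runs at ICC 0.05 and 13-27% at ICC 0.10.

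At stake is interpretation. A reader told that the trial has 95% power may take a non-significant result as evidence of no Metaverse effect, or as support for the equivalence framework named under Trial design.

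**Working it through.** **Inputs from the protocol.** N = 45, k = 3 arms, m = 4 occasions, f = 0.25, alpha = 0.05 (Sample size); equal allocation (Trial design); closed groups of 6 to 8, at least two per arm (Interventions).

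**Derived.** 45/3 = 15 per arm, so 30 in the active arms. Fifteen people in groups of 6 to 8 make two groups (average 7.5), so about four groups in all.

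**Assumed, not in the protocol.** Correlation between occasions r = 0.5, sphericity, ICC from 0 to 0.10.

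**Step 1: reproduce the stated figure.** For the within-between interaction:
- λ = f² × N × m / (1 − r) = 0.0625 × 45 × 4 / 0.5 = 22.5
- df1 = (3 − 1)(4 − 1) = 6; df2 = (45 − 3)(4 − 1) = 126
- Power = 0.9555. The minimum N is 44 (power 0.9505); 45 gives three equal arms.

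No term in this calculation refers to support groups. The result also depends on r: the required N is 53 at r = 0.4 and 36 at r = 0.6.

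**Step 2: design effect in the active arms only.** DE = 1 + (7.5 − 1) × ICC; effective N = 15 + 30/DE; λ = 0.0625 × 4 / 0.5 × effective N = 0.5 × effective N. The last column replaces 126 error df by an illustrative 48 = 3 × (14 Waitlist df + 2 group df).

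| ICC | DE | Effective N | λ | Power, 126 df | Power, 48 df |
|---|---|---|---|---|---|
| 0 | 1.000 | 45.0 | 22.5 | 0.955 | 0.937 |
| 0.01 | 1.065 | 43.2 | 21.6 | 0.947 | 0.926 |
| 0.05 | 1.325 | 37.6 | 18.8 | 0.909 | 0.882 |
| 0.10 | 1.650 | 33.2 | 16.6 | 0.864 | 0.831 |

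If groups are modelled, some power is lost through degrees of freedom even at ICC 0.

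**Step 3: a milder method.** A generalised least squares noncentrality with known variances, groups of 8 and 7 and no group effect at baseline gives the following for two time courses of the group effect:
- ICC 0.01: λ = 21.95-22.10, power 0.950-0.952
- ICC 0.05: λ = 20.10-20.72, power 0.929-0.937
- ICC 0.10: λ = 18.34-19.33, power 0.901-0.917

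**Step 4: simulation.** With the critical value recalibrated to a true 5% level and group effects growing over time, the same 6-df test has power 0.90-0.92 at ICC 0.05 and 0.83-0.87 at ICC 0.10.

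Together, steps 2 to 4 give 0.88-0.94 at ICC 0.05 and 0.83-0.92 at ICC 0.10. These ranges are not bounds. In a further known-variance calculation at ICC 0.10 that varied which active arms differ, the time course and the ICC scaling, power ran from 0.71 to 0.92. The lowest value arose when only the Metaverse arm improves and the group effect follows the same time course as the treatment effect.

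**The case against.** The strongest reply is that the calculation is right for the test it names, that the protocol gives no ICC, and that the loss at a small ICC is trivial. All of that stands. The shortfall is therefore conditional, and a reader who infers an arithmetic error, or that 0.95 is missed whatever the ICC, goes further than the documents allow. The unstated correlation between occasions also moves the required N (36 to 53 for r from 0.6 to 0.4) about as much as clustering does: restoring 0.95 at ICC 0.05 by the design-effect method takes 54.

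The counts of 30 participants and four groups are derived, not stated. The assignment section describes a simple random sequence, so exactly 15 per arm is not assured, and two groups per arm is a minimum.

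The multilevel provision shows that clustering was considered for the analysis. It does not answer the point about power.

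A reader might also infer a collapse in power for Metaverse versus Waitlist. At a difference of 1.28 SD in change, an individual-level t-test gives 0.92, and a group-level test with 1 df for the Metaverse arm gives about 0.56 at ICC 0.05 and 0.43 at 0.10. That comparison mixes two tests: the group-level test already gives 0.73 at ICC 0. Pooling the group variance over the four active groups gives about 0.75 at ICC 0.05 and 0.65 at ICC 0.10. The protocol also claims 0.95 for the overall interaction, not for this contrast.

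**Conclusion.** The point holds as an undisclosed sample-size assumption. The 0.95 is the figure for an ICC of zero, whereas two of the three arms are treated in closed groups. For an appreciable positive ICC the design does not support it: the loss is negligible at 0.01 with known variances, and power is roughly 0.88-0.94 at 0.05 and 0.83-0.92 at 0.10. This rests on about 15 per arm, two groups per active arm, r = 0.5 and an ICC range that is not in the protocol. The size of the loss is uncertain, so no single figure should be put in place of 0.95. The matter should be corrected, but it does not invalidate the trial.

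**What to change.** Keep 45. In the Sample size section:
- state that 0.95 assumes independent outcomes within support groups, and give the correlation between occasions that was used;
- report the power of the partially nested design (about two groups per active arm, individuals in the Waitlist) over a stated ICC range such as 0.01-0.10, with the ICC scaling, the time course of the group effect and the error degrees of freedom;
- state that Metaverse comparisons rest on about two groups per active arm.

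The cost is a short revision of the text and a small simulation, with no extra participants. The downside is that the stated power becomes less favourable.
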